## Abstract

**Background:**

Compared to civilians and non-medical personnel, military medical doctors are at increased risk for sleep disturbances and impaired psychological well-being. Despite their responsibility and workload, no research has examined sleep disturbances and psychological well-being among the medical doctors (MDs) of the Swiss Armed Forces (SAF). Thus, the aims of the proposed study are (1) to conduct a cross-sectional study (labeled ‘Survey-Study 1’) of sleep disturbances and psychological well-being among MDs of the SAF; (2) to identify MDs who report sleep disturbances (insomnia severity index >8), along with low psychological well-being such as symptoms of depression, anxiety and stress, but also emotion regulation, concentration, social life, strengths and difficulties, and mental toughness both in the private/professional and military context and (3) to offer those MDs with sleep disturbances an evidence-based and standardized online interventional group program of cognitive behavioral therapy for insomnia (eCBTi) over a time lapse of 6 weeks (labeled ‘Intervention-Study 2’).

**Method:**

All MDs serving in the SAF (*N* = 480) will be contacted via the SAF-secured communication system to participate in a cross-sectional survey of sleep disturbances and psychological well-being (‘Survey-Study 1’). Those who consent will be provided a link to a secure online survey that assesses sleep disturbances and psychological well-being (depression, anxiety, stress, coping), including current working conditions, job-related quality of life, mental toughness, social context, family/couple functioning, substance use, and physical activity patterns. Baseline data will be screened to identify those MDs who report sleep disturbances (insomnia severity index >8); they will be re-contacted, consented, and randomly assigned either to the eCBTi or the active control condition (ACC) (‘Intervention-Study 2’). Individuals in the intervention condition will participate in an online standardized and evidence-based group intervention program of cognitive behavioral therapy for insomnia (eCBTi; once the week for six consecutive weeks; 60–70 min duration/session). Participants in the ACC will participate in an online group counseling (once the week for six consecutive weeks; 60–70 min duration/session), though, the ACC is not intended as a *bona fide* psychotherapeutic intervention. At the beginning of the intervention (baseline), at week 3, and at week 6 (post-intervention) participants complete a series of self-rating questionnaires as for the Survey-Study 1, though with additional questionnaires covering sleep-related cognitions, experiential avoidance, and dimensions of self-awareness.

**Expected outcomes:**

Survey-Study 1: We expect to describe the prevalence rates of, and the associations between sleep disturbances (insomnia (sleep quality); sleep onset latency (SOL); awakenings after sleep onset (WASO)) and psychological well-being among MDs of the SAF; we further expect to identify specific dimensions of psychological well-being, which might be rather associated or non-associated with sleep disturbances.

Intervention-Study 2: We expect several significant condition-by-time-interactions. Such that participants in the eCBTi will report significantly greater improvement in sleep disturbances, symptoms of depression, anxiety, stress reduction both at work and at home (family related stress), and an improvement in the overall quality of life as compared to the ACC over the period of the study.

**Conclusion:**

The study offers the opportunity to understand the prevalence of sleep disturbances, including factors of psychological well-being among MDs of the SAF. Further, based on the results of the Intervention-Study 2, and if supported, eCBTi may be a promising method to address sleep disturbances and psychological well-being among the specific context of MDs in the SAF.

## Introduction

1

Findings from cross-sectional and longitudinal studies demonstrated that restorative sleep is associated with a broad variety of health benefits, including emotional and cognitive benefits and specifically, less impulsivity, enhanced driving behavior in traffic, and better social interactions. By contrast, poor sleep is associated with symptoms of depression and anxiety (1–12), low impulse control (13, 14), non-suicidal self-injury and suicidal behavior (10, 12, 15–20), impaired cognitive and emotional processing (21–36), reckless or aggressive driving behavior (37–44), and impaired social behavior (45, 46).

For short, findings from cross-sectional and longitudinal studies among children, adolescents, and adults and from non-clinical and clinical samples consistently demonstrated that impaired sleep is associated with a broad range of psychological issues on well-being, including cognitive, emotional, and social behavior problems.

### Sleep disturbances and psychological well-being among medical doctors

1.1

Medical doctors (MDs) are at increased risk of mental health issues due to low sleep quality, irregular sleeping schedules, increased latency in falling asleep and increased frequency of sleep interruptions (47–51). These issues may lead to symptoms of depression, anxiety (47–54) and burnout (54–59). To explain such impairments among MDs, research has identified long and irregular working hours, irregular sleep schedules (52, 60, 61) and stress (48, 54, 58, 59, 62–64) as main drivers associated with sleep disturbances. Given these associations, in the present study, our focus is on sleep disturbances and psychological well-being among MDs, though, among MDs in the context of the Swiss military (Swiss Armed Forces).

### Sleep disturbances among military personnel

1.2

There is sufficient evidence that compared to non-military personnel, military personnel report more sleep disturbances, in that military personnel have specific and unique work-related demands and work and life style patterns (65). Bai et al. (66) reported a number of factors that may increase sleep disturbances, especially during military operations. These include frequent involvement in high-risk activities (67), context-specific standards (65), misalignments of stable sleep–wake-rhythms, such as a disruptive sleep environment, concerns about family issues back home (68), sustained operations, excessive caffeine intake, along with the exposure to physical and psychological injuries (69). Mantua et al. (70) investigated the associations between sleep patterns and high-risk behavior among 2,296 deployed military personnel (mean age 24.7 years) and concluded that sufficient and restorative sleep may decrease poor or risky decision making in the context of military duty.

Bai et al. (66) conducted a systematic review and meta-analysis of 59 studies with a total of 28,100 participants (Ns = 14 to 8,481) involving military and veteran participants. Bai et al. (66) calculated that the overall pooled prevalence of sleep disturbances in military personnel and veterans was 69.00% (95% CI: 62.33–75.30%); pooled rates were 57.79% (95% CI: 49.88–65.50%) for active-duty personnel, and 82.88% (95% CI: 74.08–90.21%) for veterans. Further, a higher mean age, and the occurrence of symptoms of depression and posttraumatic stress disorder (PTSD) were associated with higher prevalence rates of impaired sleep. Crane et al. (71) investigated the professional and private re-integration of military personnel after their military deployment and identified adequate and restoring sleep as a key variable causally related to a favorable post-deployment process. Further factors conferring to a more successful post-deployment process were: Lower scores for shame, guilt, and negative cognitive appraisal, along with a higher motivation to deploy successfully predicted a favorable outcome in the post-deployment phase.

### Sleep disturbances among medical doctors in the military context

1.3

Regarding sleep disturbances among military MDs, research is scarce, and consistent data are lacking. Hsu et al. (72) observed that among 1,003 US Army physicians just 25% of respondents were adherent to the recommended 8 h sleep per day. When following the recommended 8 h sleep per day, about 28.4% reported a positive response to this regimen. Better sleep was associated with being a staff physician (compared to being a physician in training), and working fewer hours/week.

In a systematic review (73) summarizing 14 publications on military physicians’ sleep and professional performance, it turned out that sleep deprivation in any ‘out-of-hours’ surgery had a significant impact on overall morbidity and mortality. Sleep deprivation in surgeons and surgical trainees did negatively impact on their cognitive performance, putting their own and patients’ health at risk. More specifically, forward surgical teams will become combat-ineffective after 48 h of continuous operations (73). In a simulation study with 77 medical personnel of the Air National Guard (a federal military reserve force of the United States Air Force) it turned out that participants’ sleep quantity significantly decreased from civilian to disaster-training periods, while their cognitive performance decreased in parallel (74). In a sample of 344 medical staff members deployed to Afghanistan, they reported significantly higher levels of burnout and stress, compared to other professions (75). Adler et al. (75) did not specifically assess sleep quality or quantity; however, based on previous studies on the relation between poor sleep and increased stress (48, 62, 71, 76), we may assume that these 344 medical staff members would have reported higher scores for sleep disturbances.

Last, the National Guard (NG) served as critical component of the US COVID-19 response. A total of 3,221 NG service members were surveyed after their service in response of the COVID-19 (mean duration: 18.6 weeks). Over one-third reported changes in usual sleep: 33% described poor sleep quality, and 21% had troubles falling or staying asleep (77). This study is important in that it described the sudden shift from civil life to military life, and such sudden shifts are often observed among personnel of the SAF, in general, and among MDs of the SAF, more specifically.

Given this background, one aim of the present study was to investigate the prevalence rates of sleep disturbances (insomnia; disrupted sleep continuity) among MDs of the Swiss Armed Forces (SAF; see details below).

### Treatment of insomnia with cognitive behavioral therapy

1.4

To treat insomnia, specifically tailored CBT-interventions were established and standardized (CBTi). After a standardized and one-day long CBTi intervention, individuals with insomnia with no further mental health issues and randomly assigned to the intervention improved in their insomnia scores (78), compared to a wait-list condition. Results from meta-analyses (79–85) showed that compared to wait list or control conditions, CBTi delivered to clinical and non-clinical samples of children, adolescents and adults was always superior.

In the same vein, randomized clinical trials, and systematic review and meta-analyses evidenced that online-delivered CBTi programs (eCBTi) were as effective as ‘real’ and face-to-face CBTi interventions (86–92).

As for now, we are unaware of any eCBTi intervention to improve sleep disturbances among MDs in the military context. Given this, Intervention-Study 2 aims at investigating the feasibility and impact of a standardized eCBTi intervention on MDs of the SAF, compared to an active control condition (ACC).

### The specific context of the Swiss Armed Forces

1.5

In Switzerland, military service is mandatory for men. After basic training the most skilled recruits continue on a voluntary basis their training as cadre. After training in the non-commissioned officers’ school, the 15 weeks long officers’ school (OS) begins. This is considered to be stressful and demanding, both physically and mentally. The cadets are pushed to their limits every day during the extraordinarily intensive training. Importantly, male and female Swiss MDs in particular are encouraged to pursue the military career as military physicians.

Next, a unique aspect of the SAF is the high permeability between military and civil life. More specifically, throughout the basic military training, officers’ school, and during their annual courses, exercise trainings and refresher courses military personnel usually return home for weekends. Further, once an officer has achieved her/his rankings, annual courses and exercise trainings lasting for several days to up to 4 weeks per year are possible. At a behavioral and practical level, this implies that military MDs may switch between their private/professional and military deployments throughout their military service. Thus, the boundaries between private/civil/professional life and military life might get blurred, with quick and sometimes unpredictable transitions from civil/private/professional life to military deployments and vice versa. Such sudden changes may add to sleep disturbances. Until this date, we are unaware of studies on sleep disturbances, along with psychological well-being among MDs of the SAF. Given this, the present study aims at filling this gap of knowledge. Please consider that for the present study, exclusively medical doctors after their final exam (master’s degree) at a university were included, while officers, who did not yet complete the university degree as medical doctors were not considered.

### The concepts of the transdiagnostic approach and of allostatic load

1.6

Within the last decade two psychiatric and cognitive-behavioral concepts have gained increased attention as explanations for why the effective treatment of a specific psychiatric disorder leads to improvements in other psychiatric conditions. To illustrate, treating symptoms of insomnia also improved symptoms of depression (93), anxiety, and stress (94–99). To explain this phenomenon, the concept of the *transdiagnostic approach* (97, 100–109) reflects the observation that improvements in one dimension of psychological experiences are associated with improvements in further dimensions of psychological experiences. Moreover, a meta-analysis on the treatment of anxiety disorders did not observe systematic differences between a disorders-specific cognitive-behavioral therapy (CBT) and a transdiagnostic CBT (tCBT) (108). Further, no associations between the comorbidity rate and tCBT outcome were observed. Likewise, Brand et al. (110) showed that acute bouts of physical activity impacted positively on mood, social interaction, and rumination among inpatients with psychiatric impairments, fully irrespective from patients’ psychiatric diagnosis.

Next, the concept of *allostatic load* (111–114) may help explain the improvements of non-specific benefits of CBT. Allostatic load is understood as the cumulative effects of stressful experiences in daily life, and such an alostatic load may lead to both a physiological and psychological strain over time. Thus, it is conceivable that improvements in sleep disturbances may improve symptoms of depression, anxiety and stress, in parallel.

### The present study

1.7

Overall, there is sufficient evidence that compared to non-military personnel, military personnel report more impaired sleep, along with more issues of psychological well-being. This holds particularly true for MDs in the military context, though, research on this topic is scarce. More specifically, for MDs of the SAF, no research is available on the prevalence and association of sleep disturbances, along with concomitant issues of psychological wellbeing.

Given this background, the present study has the following aims:

Survey-Study 1: (1) To investigate the prevalence of sleep disturbances (insomnia; disrupted sleep continuity), and concomitant issues of psychological well-being among MDs of the SAF. (2) To investigate the patterns of associtions between sleep disturbances and issues of psychological well-being; (3) to identify MDs who report sleep disturbances (insomnia severity index >8), along with further dimensions of psychological ill-being and well-being such as symptoms of depression, anxiety, stress, emotion regulation, concentration, social activity, strengths and difficulties and mental toughness.

Intervention-Study 2: (3) To offer a stanrdardized online CBT program for insomnia (eCBTi). To this end, MDs reporting sleep disturbances will be randomly assigned either to the internvention condition (see details below) or to the active control condition (see details below).

For the Survey-Study 1, the hypothesis is: Higher scores for sleep disturbances are associated with more issues of psychological wellbeing such as depression, anxiety, and stress, including also social behavior.

For the Intervention-Study 2, the hypothesis is: Compared to the baseline and to an ACC, at the end of the intervention participants of the eCBTi report improved sleep disturbances, along with improved psychological well-being, as mentioned above.

## Methods

2

### Participants

2.1

We expect that all 480 MDs of the SAF complete the survey. The inclusion criteria are: 1. Aged 18 years and older; 2. Master degree or higher in human medicine; 3. MD of the SAF; 3. Willing and able to comply with the study conditions; 4. Signed written informed consent. Exclusion criteria are: 1. Completing the questionnaires in an unreliable fashion (“clickthroughts”; answers are given clicking systematically on the right or left side or in the middle; questionnaires are completed within a couple of minutes). 2. A participant withdraws from the study. 3. Pregnancy or breastfeeding, as this may alter sleep and psychological well-being. 4. A participant leaves the SAF.

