###### Insomnia

2.5.1.2.1

Participants complete the German version (116) of the Insomnia Severity Index [ISI; (117)]. The questionnaire consists of seven items that assess difficulty falling asleep, sleeping without interruption, feeling refreshed in the morning, and daytime performance, in the last 2 weeks. Participants rate how well each item describes themselves from: 0 (= not at all) to 4 (= almost always), with higher sum scores reflecting a higher degree of insomnia.

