#### Intervention

2.8.1

ANOVAs for repeated measures are run with the factors Group (eCBTi vs. ACC), Time (baseline, week 3, week 6), and the Group x Time-interaction; dependent variables as reported in Table 2. Post-hoc analyses after Bonferroni-Holm are used for p-corrections for multiple testing. Single mean comparisons are performed with Cohen’s d effect sizes, as proposed by Becker (149). In case of missing values, such missing data will be replaced with the means or medians of the sample (144, 145, 150, 151). For the intervention study: Statistical procedures are run both by protocol (that is: only available data observed at any time point from every participant are considered) and by intent-to-treat (ITT) with the last intervention carried forward (LOCF) (152). Further, we consider the following confounders, that is to say, we statistically calculate, whether the pattern of results might get biased in the same or opposite directions for the following confounders: Age, gender, working condition, including current full time or part time positions as medical doctors, including their subspeciality such as neurosurgeon, anesthesiologist, or emergency MD, to name but a few, and military rank, or time lapse between the assessment and the last deployment.

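### The only exclusion list (section 2.1) contains events that occur after randomisation; applied literally to Intervention-Study 2, it contradicts the promised ITT analysis

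*Protocol article*

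**What the plan says.** Section 2.1 (Participants) holds the article's only list of exclusion criteria. Item 2 is "A participant withdraws from the study" and item 4 is "A participant leaves the SAF". Item 1 excludes unreliable completion, and its signs are that "answers are given clicking systematically on the right or left side or in the middle; questionnaires are completed within a couple of minutes". Item 3 is pregnancy or breastfeeding. Sections 2.3 and 2.4 add reported sleep disturbance as the route into Intervention-Study 2, but no separate exclusion list is given for it.

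Section 2.8.1 says that the trial will be analysed in two ways. The first is called by protocol, where "only available data observed at any time point from every participant are considered". The second is "by intent-to-treat (ITT) with the last intervention carried forward (LOCF"). The same section adds that, where values are missing, "such missing data will be replaced with the means or medians of the sample". Section 2.7 calculates 16 participants per condition and raises this to 25 to allow for drop-out.

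**The concern.** An exclusion criterion normally decides who may enter. Withdrawal and leaving the SAF cannot be known at entry, so in this list they can act only on people already enrolled. In the randomised study that means people already allocated to eCBTi or the active control. Carrying a last value forward is useful only for participants who stop early. If those participants are excluded, the ITT set shrinks to those who stayed and LOCF has almost nothing to act on.

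The careless-response rule raises the same difficulty. It refers to the questionnaires in general, and Table 1 repeats many of them at weeks 3 and 6. As worded, it could exclude a randomised participant on the basis of outcome data.

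What is at stake is the protection that randomisation gives. An analyst who must choose between section 2.1 and section 2.8.1 after seeing the data could justify either set. There is also reason to think that drop-out could differ between arms. The eCBTi arm has sleep restriction (Table 2) and 60 to 90 minutes of homework a week (section 2.6.1). The control arm has group discussion and journaling (section 2.6.2) and may switch to eCBTi at the end (section 2.4), which is a reason to stay.

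**Working it through.** **1. The passages side by side**

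| Question | Section 2.1 read literally | Sections 2.7 and 2.8.1 |
|---|---|---|
| Randomised, then withdraws | Excluded | In the ITT set, last value carried forward; drop-out allowed for in N |
| Randomised, then leaves the SAF | Excluded | As above |
| Randomised, week 3 or 6 answers look careless | Excluded | No such removal mentioned |

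Neither section says which one governs.

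**2. The plan's own sample size**

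Inputs from section 2.7: partial eta-squared 0.08, alpha 0.05, power 0.95, 2 groups, 3 measurements, N = 32. Assumed because not stated: correlation between measurements 0.5 and sphericity (the G*Power defaults).

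- f² = 0.08 / 0.92 = 0.087, so f = 0.295.
- λ = N × f² × 3 / (1 − 0.5) = 32 × 0.087 × 6 = 16.7, with 2 and 2 × (32 − 2) = 60 degrees of freedom.
- Power = 0.955, so N = 32 reproduces.
- With all 50 randomised participants kept, power is 0.997. If the correlation is 0.3, power is 0.864 at N = 32 and 0.975 at N = 50.

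The stated N is therefore not the issue. The gap between 25 and 16 per arm is (25 − 16) / 25 = 36%. This is the headroom that the plan allows, not a drop-out rate that it predicts.

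**3. What removing drop-outs could do (illustration)**

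Assumptions, none from the document: 25 per arm, no true effect, one normally distributed outcome in SD units with higher meaning better, a two-sample t-test at 0.05, and a latent tendency to drop out that correlates r with poor outcome. If a fraction d of an arm drops out and is removed, the mean of those who remain shifts upward by

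r × φ(c) / (1 − d), where c is the standard normal quantile at 1 − d.

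- d = 0.36: c = 0.358, φ(c) = 0.374, ratio 0.374 / 0.64 = 0.585.
- d = 0.20: c = 0.842, φ(c) = 0.280, ratio 0.280 / 0.80 = 0.350.
- d = 0.10: c = 1.282, φ(c) = 0.175, ratio 0.175 / 0.90 = 0.195.

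The bias is r times the difference between the arms' ratios. Type I error comes from simulation.

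| Drop-out, arm 1 vs arm 2 | r | Bias (SD) | Type I error |
|---|---|---|---|
| 36% vs 36% | 0.3 or 0.5 | 0 | about 0.05 |
| 36% vs 10% | 0.3 | 0.3 × 0.390 = 0.12 | about 0.07 |
| 36% vs 10% | 0.5 | 0.5 × 0.390 = 0.20 | about 0.09 |
| 20% vs 10% | 0.3 | 0.3 × 0.155 = 0.05 | about 0.05 |
| 20% vs 10% | 0.5 | 0.5 × 0.155 = 0.08 | about 0.06 |
| 36% vs 10% | 0 | 0 | about 0.05 |

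The simulated biases agree with the formula to within 0.01 SD. Bias needs both conditions: drop-out unequal between arms, and drop-out related to outcome. It favours the arm that loses more poor responders.

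**4. The careless-response rule and the survey prevalence**

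The ISI has seven items scored 0 to 4 (section 2.5.1.2.1). Uniform left, middle and right answers give 7 × 0 = 0, 7 × 2 = 14 and 7 × 4 = 28. Only the first is a non-case at the threshold of above 8. With an assumed true prevalence of 33% and 10% of respondents removed:

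- all of those removed are non-cases: 0.33 / 0.90 = 36.7%;
- all of those removed are cases: (0.33 − 0.10) / 0.90 = 25.6%.

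The document does not settle the direction.

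**The case against.** The best defence is that section 2.1 does not say that anyone's data are deleted. Excluded may mean only that participation ends. The section that governs analysis points that way: LOCF presupposes that early leavers are kept, the by-protocol analysis uses available data from every participant, and the sample is enlarged for drop-out. It can also be said that section 2.1 opens with the 480-person survey and contains no insomnia criterion, so it may be the survey's list alone. Both readings are possible, and they are why this is a conflict to reconcile and not an established loss of data. They do not remove the point: no other exclusion list exists for the trial, and nothing in the text limits this one to the survey or ranks the two sections.

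A reader might go further and infer that the click rule removes healthy respondents who validly answer zero throughout, so that insomnia prevalence is overstated. The ISI wording ("Participants rate how well each item describes themselves from: 0 (= not at all) to 4 (= almost always")) makes uniform zeros a valid answer on that one scale. But the rule is aimed at unreliable completion of the questionnaires as a whole. That booklet includes scales on which high scores are favourable (SASS, section 2.5.1.9; mental toughness, section 2.5.1.11) and a sleep questionnaire that asks for times and counts (section 2.5.1.2.2). The rule would also remove middle and right clickers, who count as cases. Neither the removal of valid responders nor an upward bias can be derived from the text. The missing threshold and scope are mostly detail that an article may leave to the full protocol.

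A reader might also take 36% as the expected loss, or take bias as certain. The documents support neither.

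**Conclusion.** The point holds as a contradiction between section 2.1 and sections 2.7 and 2.8.1. Two post-enrolment events, and a response-quality rule not confined to the period before randomisation, stand as exclusion criteria in a project that promises an ITT analysis of its randomised part. The group comparison can be biased if they are applied literally and if drop-out is both unequal and outcome-related. In the illustration this is about 0.12 to 0.20 SD with type I error of about 0.07 to 0.09 at 36% against 10%, 0.05 to 0.08 SD with little change in type I error at 20% against 10%, and about nothing when drop-out is equal. These sizes rest on assumed drop-out rates and correlations. The sample size reproduces and is not affected. No conclusion about the direction of any error in the survey prevalence is warranted.

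**What to change.** Reconcile sections 2.1 and 2.8.1 as follows.

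- Take items 2 and 4 out of the exclusion criteria and describe them as reasons for discontinuation.
- State that all randomised participants form the ITT set, in the arm to which they were allocated, and that data collected up to discontinuation are kept as far as consent allows. The consent terms are not shown, so this limit must be checked.
- Apply the careless-response exclusion only before randomisation. Keep flagged records from later visits in the main analysis, and examine their influence in a sensitivity analysis.
- Pregnancy (item 3) can also begin after randomisation, so say what it means for the analysis set.
- Optionally, report the survey prevalence with and without flagged records.

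The cost is a few sentences and one extra sensitivity analysis; no new data are needed. The downside is that a few careless records may remain in the ITT set.
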